## 5.2 Control Arm

| Actions and Instruments                                                                                                                                                                                                                                                                                                                                                                                                              | Baseline a | 12 Months |
|--------------------------------------------------------------------------------------------------------------------------------------------------------------------------------------------------------------------------------------------------------------------------------------------------------------------------------------------------------------------------------------------------------------------------------------|-----------------------|-----------|
| Information provided; recruit to study; consent form; GDPR Data form, visit to survivorship clinic, meet dietician- dietetics assessment (e.g. BMI, diet)
Baseline: patient clinical and socio-demographics collected                                                                                                                                                                                                             | X                     | X         |
| Randomisation                                                                                                                                                                                                                                                                                                                                                                                                                        | X                     |           |
| Current medications                                                                                                                                                                                                                                                                                                                                                                                                                  | X                     | X         |
| Comorbidities                                                                                                                                                                                                                                                                                                                                                                                                                        | X                     | X         |
| ePRO Health related-Quality of Life survey. Instruments used as follows:
1. EORTC-QLQ-C30 (30 items) ±
2. Considering patients cancer type:
• Cervical cancer: EORTC QLQ – CX24 (24 items)
• Endometrial cancer: EORTC QLQ – EN24 (24 items)
• Breast cancer: EORTC QLQ - BR23 (23 items)
3. EQ-5D-5L (5 items) (measures QALY)
4. Appraisal Self-Care Agency-R (15 items) (measures power to self-care) | X                     | X         |
| ePRO Patient-reported symptom questionnaire includes -PROMIS and PRO-CTCAE items
Fear of cancer recurrence, Adherence                                                                                                                                                                                                                                                                                                             | X                     | X         |
| Body weight                                                                                                                                                                                                                                                                                                                                                                                                                          | X                     | X         |
| BIA measurement                                                                                                                                                                                                                                                                                                                                                                                                                      | x                     | x         |
| Hand-grip strength                                                                                                                                                                                                                                                                                                                                                                                                                   | x                     | x         |
| Diet intake assessments
(multiple 24hour dietary recalls & food frequency questionnaire)                                                                                                                                                                                                                                                                                                                                          | x                     | x         |
| Diet quality assessment
(World Cancer Research Fund / American Institute for Cancer research score)                                                                                                                                                                                                                                                                                                                               | x                     | x         |
| Use of resources form                                                                                                                                                                                                                                                                                                                                                                                                                |                       | X         |
| End of study patient questionnaire—includes system usability, satisfaction scales                                                                                                                                                                                                                                                                                                                                                    |                       | X         |
| Clinician/stakeholder questionnaires                                                                                                                                                                                                                                                                                                                                                                                                 |                       | X         |
| Qualitative interviews with patients, healthcare professionals and wider team
(process evaluation)                                                                                                                                                                                                                                                                                                                                |                       | X         |
| Clinician record of actions/follow-up at survivorship and symptom management encounters
Data extracted from hospital records                                                                                                                                                                                                                                                                                                      |                       | X         |
| Drop out date, reason (data collected as required)                                                                                                                                                                                                                                                                                                                                                                                   |                       |           |

- a. Baseline measures may be completed up to 2 weeks after enrollment and prior to attendance at the initial clinic visit. Electronic survey reminders will be sent to patients to facilitate ePRO completion

Note: Clinical follow-up will be according to standard of care. Follow-up visits are not specifically required per protocol other than those needed for routine clinical care.

## 6.0 Statistical Plan

---

Once data entry is finalized, study data will be assessed for incompatible, discrepant or clinically implausible values. Outlying values for all distributions, in isolation and over time, will be identified. Any concerning data will be reconciled against original source data. Following completion of cleaning the database will be locked and the randomization code will be released.

The study sample will be described in detail. Continuous variables will be described by their means and SDs, medians and IQRs, and their range; while categorical variables will be described by their counts and percentages in each category.

Feasibility outcomes will be similarly described. These include the number of enrolled patients who complete the baseline and follow-up ePRO surveys, and the number of patients who partake in the healthcare professional consultation after ePRO data triggers such as a review/consultation; the number of patients that require medical review and the timeframe to Medical review; the average consultation time; the number of patients enrolled in the clinic; extra Health Care Professional time required and resources required for the intervention; and reasons for not completing the intervention will be collected through Drop Out Forms and with qualitative discussions with HCP involved in the clinic.

Between-group patient-relevant outcome differences, which can be used to inform a subsequent efficacy trial, will generally be estimated using generalized linear models with link functions based on the outcome for a given model, and a random effect for patient when relevant (e.g. longitudinally measured outcomes). All model-based estimates will be reported with 95% CIs and exact p-values. Missing data will be evaluated, and based on what we observe, dealt with in whatever manner we find appropriate based on current best practices. All analyses will be conducted using the R Project for Statistical Computing and the RStudio IDE. All trial reporting will be done following CONSORT and the CONSORT addendum for pilot/feasibility trials (Eldridge et al, 2016)

All analyses will be conducted and/or supervised by the HRB CRF-C Principal Statistician ([name]), under their established quality systems and SOPs, and in accordance with *ICH E9 Statistical Principles for Clinical Trials* and *ICH E6 Good Clinical Practices*.

## 7.0 Safety and Adverse Events

---

### 7.1 Recording of Adverse Events

It is not anticipated that any study related adverse events will occur during the study. This is an observational project involving collection of data regarding breast and gynaecological cancer care administered in accordance with this protocol. Information related to toxicities from adjuvant therapy will be collected as described above through ePRO measures, but these will not be considered adverse events. We do not anticipate any adverse events associated with completion of the ePRO modules. Patients will have the option of skipping questions they do not wish to answer. In event that study participation does result in any event that has negative consequences for the subject, this will be recorded by the PI in the EDC (Electronic Data Capture) and will be reported to the Sponsor and Ethics committee.

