| Study Design                | Complex interventional study                                                                                                                                                                                                                                                                                                                                                                                                                                                                                                                                                            |                                |                                                                                                                                                  |
| Specific Aims               | To evaluate the feasibility of introducing a women's malignancy survivorship clinic incorporating symptom management through ePRO collection (complex intervention) into routine follow up care in patients with early-stage HR-positive breast and gynaecologic cancer post primary therapy                                                                                                                                                                                                                                                                                            |                                |                                                                                                                                                  |
| Sampling Method             | Randomized Control Design (Parallel Arms)                                                                                                                                                                                                                                                                                                                                                                                                                                                                                                                                               |                                |                                                                                                                                                  |

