## 3.0 Study Plan

### 3.1 Design:

Complex interventional clinical study.

This randomized controlled clinical trial (RCT) will be conducted to test both the 1) Feasibility of conducting a Women's Malignancy Survivorship Clinic in Ireland, in women with HR-positive breast cancer and gynaecologic cancer post primary curative therapy and 2) The hypothesis that female cancer survivors who participate in a survivorship clinic intervention incorporating ePRO collection and targeted symptom management are more likely to experience improvement in symptom burden and QOL compared to controls who did not receive partake in the targeted symptom management pathways.

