### 4.2 Sample size justification

Given that the main objectives of this study are to evaluate the *feasibility* of introducing a women's malignancy survivorship clinic, we have not calculated the sample size that would be required to reliably estimate the effect of the clinic on patient outcomes. This follows from established best practices in pilot and feasibility studies (Whitehead, Sully, & Campbell, 2014) for which there is usually too much uncertainty in the various factors that are needed to make a sample size calculation robust (e.g. effect sizes of interest, outcome variability, etc.). Our sample size justification is instead based on trying to recruit the largest possible sample given existing financial and pragmatic constraints. This will allow us to maximize our ability to identify barriers to implementation, as well as the information that will be required to properly design any subsequent trials of the clinic's efficacy (e.g. robust estimation of estimator variability, even for binary outcomes (Teare, Dimairo, Shepard et al., 2014)). At the same time, the potential costs of over-recruitment are largely absent for this study. Most importantly, there are no excess risks to patients receiving the intervention, and all patients are guaranteed access to the current standard of care. Further, most of the financial costs of the study are fixed, regardless of the actual number of

patients recruited into the study. With these points in mind, based on the current numbers of patients coming through existing services, we anticipate recruiting approximately 140 patients with early stage breast cancer from the Orchid Centre in Cork University Hospital over the first 12 months of the study (approximately 3 patients per week). We further anticipate being able to recruit 60 patients with cervix/endometrial cancer over the 12 month period (approximately 1 each week). This will amount to approximately 200 patients, which will leave us in an excellent position to meet the objectives of the study (Viechtbauer, Smits, Kotz, et al., 2015; Whitehead, Julious, Cooper & Campbell, 2016).

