### **Nutrition for the intervention arm**

The nutrition intervention will include a personalised approach to nutrition education for patients in the intervention arm only. Patients will complete a symptom survey at 2 monthly intervals throughout the study. The symptom survey will act as screening tool to identify nutritional risk. Patient specific nutrition counselling will be offered to patients identified at risk.

***Diet Education and Personalised Nutrition Counselling:*** The main goal of the nutritional intervention is to improve the diet quality of each patient using a standardized nutrition assessment, offering evidence-based diet education and developing personalized nutrition goals. Individual goals and targets will be set during the 1st consultation. Dietary counselling involves the prescription of a therapeutic diet that uses regular foods, which can be further modified to provide for individual requirements. The therapeutic diet is adjusted to the individual's usual diet, thereby recognizing personal eating patterns and preferences, which form the basis for individualized dietary counselling. The prescription identifies the type, amount, and frequency of feeding and specifies the caloric/protein level to attain, together with any restrictions and limited or increased individual dietary components. In addition, nutritional advice can be adapted to respond to specific nutrition impact on symptoms (e.g. dysphagia, constipation, diarrhoea, altered taste and temperature sensitivity). Energy and protein requirements will be calculated only for patients that require specific caloric and protein targets to meet their individualised nutritional goals.

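### Section 7.1 calls a randomised intervention trial observational and records adverse events only when attributed to participation, so those records alone cannot support the no-excess-risk statement in 4.2

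*Protocol*

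**What the plan says.** On design, the Study Synopsis gives "Randomized Control Design (Parallel Arms" as the sampling method, and section 3.1 opens with "This randomized controlled clinical trial (RCT) will be conducted to test both the 1) Feasibility". The safety section, 7.1, instead says: "This is an observational project involving collection of data regarding breast and gynaecological cancer care administered in accordance with this protocol".

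On recording, 7.1 expects no study-related adverse events. It notes that toxicities of adjuvant therapy will be gathered through the ePRO measures, "but these will not be considered adverse events". Its one rule for making a record is: "In event that study participation does result in any event that has negative consequences for the subject, this will be recorded by the PI". The record goes into the electronic data capture system and is reported to the sponsor and the ethics committee.

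On risk, section 4.2 argues for the largest sample that resources allow, and its leading reason why over-recruitment would do little harm is that "there are no excess risks to patients receiving the intervention".

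On the intervention, sections 4.3 and 4.4.6 describe nurse-led symptom pathways driven by ePRO alerts, specialist referral and, in the intervention arm only, personalised dietetics: "Dietary counselling involves the prescription of a therapeutic diet that uses regular foods".

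**The concern.** The safety section describes a different kind of study from the one being run. In an observational study, with no assigned treatment, there is little reason to ask whether harms differ by arm. Here patients are randomised to receive or not receive symptom pathways, referral and dietary prescription, so that question is a proper one.

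The recording rule has the same weakness. If an event must first be held to result from participation, someone decides causation before any record exists, and the protocol gives no criteria for that decision. An event put down to the disease or to usual care never enters the adverse event record of either arm. A low or zero count could then reflect the filter rather than the absence of harm.

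Two statements elsewhere depend on this. Section 4.2 uses the absence of excess risk to help justify the sample size. Section 2.1 plans to offer the clinic to all patients as standard care if it proves feasible. A later analysis plan could not repair the gap, because it cannot recover events that the protocol never had recorded.

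**Working it through.** No arithmetic decides this point, so the check sets the relevant sections side by side. The protocol's one size figure, 140 breast plus 60 cervix/endometrial = 200 patients (section 4.2), reproduces, but it rests on recruitment and not on any event rate.

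1. **Design label.** Synopsis: randomised, parallel arms. Section 3.1: randomised controlled trial of a complex intervention. Section 7.1: observational. All three are current text, and they cannot all be right.

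2. **Order of attribution and recording.** Under 7.1 a record follows only if participation led to the event. Section 4.4.3 conceals each allocation from the research team until the patient is enrolled, so it may be known from then on. Section 6.0 releases the randomisation code after database lock, but neither section describes masking the investigator who records events. The attribution is therefore made without described masking, and before recording.

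3. **Contact by arm** (sections 4.3, 4.4.5, 5.1 and 5.2).
   - Intervention: symptom surveys at baseline and months 2, 4, 6, 8, 10 and 12, which is 7, plus a nurse call at month 6.
   - Control: symptom surveys at baseline and month 12, which is 2.
   - Resource use: collected continuously in the intervention arm and at the end of the study in the control arm.
   - Clinician actions and hospital-record data: months 2 to 12 in the intervention calendar (6 time points) and month 12 only in the control calendar (1 time point).

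   Events that come to notice through contact have more chances of being noticed in the intervention arm.

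4. **What both arms supply without a causality filter.**
   - PROMIS and PRO-CTCAE symptoms, comorbidities, medications, body weight, body composition and grip strength, at baseline and month 12 (sections 4.4.5, 5.1 and 5.2).
   - Drop-out date and reason (5.1 and 5.2). Possible reasons include death, recurrence and intercurrent illness (4.4.9).

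   Section 6.0 plans between-group estimates of patient-relevant outcomes. A limited comparison of harm at 12 months is therefore possible.

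5. **What remains uncovered.** Both calendars carry a line for "Data extracted from hospital records", but sections 4.4.5 and 4.4.11 describe the Cork University Hospital extraction as baseline clinical details, current medications and the survivorship services used. They describe the patient diaries as a record of services used elsewhere. Neither names unplanned admissions or emergency attendances. Death, recurrence and intercurrent illness are named only as possible reasons for discontinuing. A patient who is admitted and stays in the trial therefore has no stated route into a safety record, unless the admission is attributed to participation.

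**The case against.** The strongest reply is proportionality. This is a feasibility study of nurse-led follow-up and dietary advice. The absence of excess risk is a premise of the sample-size argument, not an objective or an endpoint, and the trial never undertakes to test it. Death and recurrence leading to discontinuation are already documented and can be counted by arm whatever their cause. Tabulation by arm is ordinary analysis-plan content, and that plan is not shown. The Nurse Record Form, use-of-resources form and diaries are not shown either, and they might capture admissions. All of this stands, and it narrows the point. It does not remove the contradiction between 7.1 and 3.1, or the attribution-first rule.

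Three stronger readings are tempting, and the protocol does not support them:

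- **That the trial has no means of checking for excess harm.** The both-arm data in step 4 of the working allow a partial check. For the dietary component in particular, weight, body composition and grip strength are measured in both arms at both time points.
- **That 7.1 considers only the risk of completing questionnaires.** That is one sentence among several. The section opens with study-related adverse events in general, and its recording rule covers any negative consequence of participation. The toxicities it sets aside are those of adjuvant therapy, which is background treatment, and they are still collected.
- **That the loss can be put as a number, for example an upper limit on the event rate when none is recorded.** That would need the number per arm and the share of events the rule lets through. The protocol states neither an allocation ratio nor a capture rate. A single-arm limit would in any case not measure excess risk, which is a difference between arms.

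**Conclusion.** The point holds in limited form. Section 7.1 misdescribes the design and makes attribution a condition of recording. The resulting adverse event records are filtered by a judgement for which no masking is described and are exposed to unequal contact. They cannot by themselves support the statement in 4.2.

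The size is moderate and cannot be quantified from the protocol. The primary endpoint, ePRO completion, is unaffected. The specific hole is unplanned admissions and emergency attendances, together with any recurrence or serious illness that does not lead to discontinuation. The change should be made, but the trial does not fail without it.

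This rests on two assumptions: that the investigator making the attribution can know the allocation, since no masking is described after enrolment; and that the forms not shown collect no more than the protocol says. If the Nurse Record Form or the diary already lists admissions regardless of cause, the remaining work is to reconcile the wording and to say that those entries will be used.

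**What to change.** 1. In 7.1, replace the observational description with the randomised interventional design of section 3.1, so that the Synopsis, 3.1 and 7.1 agree.
2. Add fields to the month-12 record review and diary collection in both arms to list every death, recurrence, unplanned hospital admission and emergency attendance, regardless of attribution. Cover all randomised patients as far as consent allows, including those who discontinued, since 4.4.9 keeps everyone who starts the study in the overall analysis.
3. Judge relatedness after listing, and tabulate by randomised arm from this common month-12 source only. Events noticed through the two-monthly surveys or the nurse call should not enter the between-arm table by that route alone.
4. In 4.2, reword the statement on excess risk as an expectation that the trial will examine.

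The cost is protocol wording, a few added form fields and modest abstraction time. The extraction as now described covers baseline clinical details, current medications and survivorship services, so looking for admissions and attendances is some additional work. No visit is added and clinical management does not change.
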